## Abstract

**Background:**

Approximately 20% of patients with ulcerative colitis become steroid dependent. Azathioprine is recommended in steroid-dependent ulcerative colitis, but its side effects limit its use. Chinese herbal medicine has been widely used to treat ulcerative colitis in China. However, its effectiveness in steroid-dependent patients has not been evaluated. This study aims to investigate the efficacy of traditional Chinese medicine combination therapy with 5-aminosalicylic acid in patients with steroid-dependent ulcerative colitis.

**Methods/Design:**

This is a parallel, multicenter, randomized controlled trial. One hundred and twenty eligible patients will be randomly assigned to a traditional Chinese medicine group or azathioprine group. All patients will be given basic treatment, which includes steroids and 5-aminosalicylic acid. Patients allocated to the traditional Chinese medicine group will receive basic treatment plus Chinese herbal medicine granules, while patients in the azathioprine group will receive basic treatment plus azathioprine. The whole study will last 24 weeks. The primary outcome measure is the steroid-free remission rate. Secondary outcome measures are health-related quality of life, efficacy of endoscopic response, degree of mucosal healing, and inflammation indicators.

**Discussion:**

Results from this study may provide evidence for the effectiveness of traditional Chinese medicine combined with 5-aminosalicylic acid in patients with steroid-dependent ulcerative colitis. The findings will provide a basis for further confirmatory studies.

**Trial registration:**

Chinese Clinical Trial Register, ChiCTR-IPR-15005760. Registered on 2 January 2015.

**Electronic supplementary material:**

The online version of this article (doi:10.1186/s13063-016-1763-9) contains supplementary material, which is available to authorized users.

## Background

Ulcerative colitis is a form of inflammatory bowel disease characterized by a chronic relapsing clinical course. Intermittent rectal bleeding, diarrhea, and abdominal pain are often symptoms of ulcerative colitis. 5-Aminosalicylic acid is usually used in mild cases of ulcerative colitis. Steroids are another effective therapy for inducing remission in patients with moderate and severely active ulcerative colitis. Approximately 20–34% of patients with ulcerative colitis have chronic active disease requiring several courses of steroids to achieve remission [1, 2]. Many patients initially benefit from steroid treatment but relapse shortly after treatment cessation or after dose reduction. Up to 20% of patients with ulcerative colitis become steroid dependent [3]. The European Crohn’s and Colitis Organisation guidelines define “steroid-dependent” patients as those who are unable to reduce steroids below the equivalent of prednisolone 10 mg/day within 3 months of starting steroid use, without recurrent active disease, or who have a relapse within 3 months of stopping steroid use [4]. The risks of long-term steroid therapy include osteoporosis, pathological fractures, cataracts, metabolic changes, psychological disturbances, and infection. Moreover, steroids have not been shown to be effective for the maintenance of remission.

The American College of Gastroenterology and European Crohn’s and Colitis Organisation guidelines recommend that patients with steroid-dependent disease should be treated with azathioprine or 6-mercaptopurine [5, 6]. Azathioprine is significantly more effective than 5-aminosalicylic acid at achieving clinical and endoscopic remission in the treatment of steroid-dependent ulcerative colitis. In a single-center retrospective cohort study, 64 Asian patients with steroid-dependent inflammatory bowel disease were assessed, and 61% of patients were able to maintain clinical remission after 5 years of azathioprine therapy [7]. Toxicity induced by azathioprine and 6-mercaptopurine in patients with inflammatory bowel disease includes bone marrow suppression, drug-induced hepatitis, pancreatitis, and infection.

Complementary and alternative medicine use is common in patients with inflammatory bowel disease. The single most commonly used modality in most surveys is traditional Chinese medicine (TCM) [8]. Chinese herbal medicine is useful in improving symptoms, such as abdominal pain and diarrhea, and reducing inflammation in patients with ulcerative colitis. Many steroid-dependent patients are dissatisfied with conventional therapies, including azathioprine’s side effects; thus, they turn to TCM. However, it is not clear whether Chinese herbal medicine is effective for patients with steroid-dependent ulcerative colitis. Therefore, the primary aim of our study is to evaluate the clinical efficacy of TCM treatment among patients with steroid-dependent ulcerative colitis. Health-related quality of life in steroid-dependent patients will be a secondary aim.

## Methods/Design

This is a multicenter, randomized controlled trial with two parallel groups and a 24-week follow-up. The centers include the Affiliated Hospital of Nanjing University of Chinese Medicine, Beijing Hospital of Chinese Medicine, Guangdong Province Hospital of Chinese Medicine, Longhua Hospital affiliated to Shanghai University of Chinese Medicine, the First Affiliated Hospital of Henan University of Chinese Medicine, Nanjing Drum Tower Hospital of Nanjing University of Medical School, Shengjing Hospital of China Medical University, the Hospital of Shanxi University of Chinese Medicine, the First Affiliated Hospital of Heilongjiang University of Chinese Medicine, and Nantong Hospital of Chinese Medicine. The study began in January 2015 and will last until October 2017. Trained researchers enroll participants. One hundred and twenty patients who meet the eligibility criteria will be recruited and allocated into two groups, with 60 individuals per group. This study has been approved by the Institutional Review Board of Human Research of the Affiliated Hospital of Nanjing University of Chinese Medicine (approval number: 2014NL-073-03). Participants must provide written informed consent to participate in the study. All participants will continue their initial steroid and 5-aminosalicylic therapy, and will be randomly assigned to receive either Chinese herbal medicine or azathioprine. The overall flow of the trial is shown in Fig. 1.

**Fig. 1 Fig1:**
[figure not shown]
Flow chart of the trial. 5-ASA, 5-aminosalicylic acid; AZA, azathioprine

### Eligibility criteria

Participants will be considered for enrollment if they: range in age from 18 to 65 years; have a confirmed diagnosis of steroid-dependent ulcerative colitis; agree to participate in this clinical trial; and sign the informed consent form.

Patients will be excluded from the study if they: experience complications such as intestinal obstruction, intestinal perforation, toxic megacolon, or colorectal cancer; are pregnant, breast-feeding, or preparing for pregnancy; have an alanine aminotransferase level above the twice upper limit of normal; have a serum creatinine level above the upper limit of normal; have a platelet value of less than 50 × 10^9^/l; have a leukocyte count of less than 3.0 × 10^9^/l; have a known history of alcohol or drug abuse; or are enrolled in other clinical trials.

### Sample size

The remission rate for ulcerative colitis by azathioprine ranges from 59.1% to 87% [9, 10], and the average rate is about 73%. This is a noninferiority trial. For a two-sided significance level of 0.05 and power of 80% (*α* = 0.05, *β* = 0.2, *δ* = 0.15), the sample size is calculated using the formula:$$ n=12.365\times P\left(1-P\right)/{\delta}^2 $$

Considering a 10% loss to follow-up, the sample size is 120 cases (*n* = 60 in each group).

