### Outcome measures

#### Primary outcome measure

The primary outcome measure of this study is the steroid-free remission rate in patients with steroid-dependent ulcerative colitis. Remission is defined as a Mayo disease activity index score of 0–2, with no individual subscore exceeding 1 [14]. The withdrawal time of steroids will also be recorded. The outcome measure will be evaluated at the end of 24 weeks. If there is no statistical significance between the steroid-free remission rate of the TCM group and the azathioprine group, then the mean withdrawal time from steroids will be compared.

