In view of the side effects of steroids, different drugs are used in the management of steroid-dependent ulcerative colitis. Drugs used include established agents, such as thiopurines, methotrexate, infliximab, adalimumab, vedolizumab, and golimumab. If common treatments fail, colectomy may be performed [16]. Current guidelines recommend thiopurines as first-line therapy to spare steroids in steroid-dependent ulcerative colitis [3, 6]. Therefore, the thiopurine agents azathioprine and 6-mercaptopurine are used to sustain steroid withdrawal in patients with steroid-dependent ulcerative colitis [5]. Azathioprine is a purine analog that competitively inhibits the biosynthesis of purine ribonucleotides [17]. Azathioprine is the main therapy for steroid-dependent patients in China, because vedolizumab and golimumab are not available, and adalimumab is not indicated for use in patients with ulcerative colitis. Furthermore, cessation of infliximab is still considered in clinical practice because of its high cost and fear of long-term side effects [18]. There is also a reduced response to infliximab, which may reach approximately 13% per year with uninterrupted scheduled maintenance therapy [19]. Fraser *et al.* reported that the remission rate was 87% in 346 ulcerative colitis patients who received more than 6 months of azathioprine treatment [10]. Another study demonstrated that the steroid-free remission rate was 59.1% in patients with steroid-dependent or steroid-resistant ulcerative colitis treated with azathioprine [9]. The most common adverse event of azathioprine is leukopenia, which occurs in 3.8% of patients [20]. Other adverse events include hepatitis, infection, pancreatitis, and hair loss. Once absorbed into the plasma, azathioprine is nonenzymatically converted to 6-mercaptopurine. 6-Mercaptopurine can be metabolized to 6-methylmercaptopurine by the enzyme thiopurine methyltransferase (TPMT), to 6-thiouric acid by the enzyme xanthine oxidase, and to the active metabolites of 6-thioguanine nucleotide. 6-Thioguanine nucleotide is the active ribonucleotide of 6-mercaptopurine; it functions as a purine antagonist, resulting in immunosuppression and lymphocytotoxicity. A deficiency in TPMT may lead to preferential 6-mercaptopurine metabolism into 6-thioguanine nucleotide, resulting in myelosuppression [21]. An apparent genetic polymorphism of TPMT is associated with TPMT enzyme deficiency. Despite a lower frequency of variant TPMT observed in Asian populations [22], lower starting doses of azathioprine are recommended in Asian populations than in white populations, along with close monitoring of complete blood count and liver function [13].

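### The 73% planning rate is the midpoint of two azathioprine rates that the article describes as different quantities; the closer one, 59.1%, needs about 23% more patients and lowers power by about 7 points

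*Protocol article*

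**What the plan says.** The Sample size section of the protocol article takes its azathioprine rate from two cited sources: "The remission rate for ulcerative colitis by azathioprine ranges from 59.1% to 87% [9, 10], and the average rate is about 73" per cent. It gives no reason for averaging them. It then declares "This is a noninferiority trial" and sets a margin of 0.15, two-sided 0.05 and 80% power. The formula is n = 12.365 × P(1 − P)/δ², and with 10% loss the section arrives at 120 patients, 60 per group.

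The Discussion describes the same two sources more fully. For one, "the remission rate was 87% in 346 ulcerative colitis patients who received more than 6 months of azathioprine treatment". For the other, "the steroid-free remission rate was 59.1% in patients with steroid-dependent or steroid-resistant ulcerative colitis treated with azathioprine".

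The trial's own target is set under Primary outcome measure: "The primary outcome measure of this study is the steroid-free remission rate in patients with steroid-dependent ulcerative colitis", and "The outcome measure will be evaluated at the end of 24 weeks". Eligibility criteria require that patients "have a confirmed diagnosis of steroid-dependent ulcerative colitis". The statistical section specifies an intention-to-treat analysis.

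**The concern.** A planning rate should estimate what the control arm will show on this trial's endpoint, in this trial's patients. The Sample size section puts both figures under one label, remission on azathioprine, but by the Discussion's account they are not the same quantity. The 59.1% is steroid-free remission in steroid-dependent or steroid-resistant disease. The 87% is not described as steroid-free, its patients are not described as steroid-dependent, and they are described as having received more than 6 months of the drug. An intention-to-treat analysis at 24 weeks also counts patients who stop early. A group defined by staying on treatment would be expected to show a higher rate.

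The choice matters because the margin is a fixed 15 points. The variance term P(1 − P) grows as P approaches 0.5. If the true control rate is nearer 59% than 73%, the trial needs more patients, and the patients it has give less power. Correcting the other errors in the calculation while keeping 73% would still leave the trial short.

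**Working it through.** **Inputs.** From Sample size: margin 0.15, constant 12.365, 80% power, two-sided 0.05, 10% loss, 60 per group. From Sample size and Discussion: rates 59.1% and 87%.

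**1. Where 73% comes from.** (59.1 + 87)/2 = 73.05, an unweighted midpoint.

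**2. The article's own figure.** 12.365 × 0.73 × 0.27/0.0225 = 108.3, so 109. Multiplying by 1.1 gives 119.9, which is the stated 120; dividing by 0.9 gives 122. But 12.365 = 2(1.645 + 0.842)², the per-group constant for one-sided 0.05. So 109 is a number per group, and 120 results only if it is read as the total. For noninferiority at two-sided 0.05 (one-sided 0.025) the constant is 2(1.960 + 0.842)² = 15.698.

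**3. Required number per group.** P(1 − P) is 0.1971 at 0.73 and 0.2417 at 0.591, a ratio of 1.23.

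| Level | P = 0.73 | P = 0.591 | With 10% loss (÷ 0.9) |
|---|---|---|---|
| One-sided 0.05 (constant 12.365) | 109 | 133 (132.8) | 122 against 148 |
| Two-sided 0.05 (constant 15.698) | 138 | 169 (168.6) | 154 against 188 |

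**4. Power of the planned trial.** With equal true rates, SE = √(2P(1 − P)/n) and power = Φ(0.15/SE − z).

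- 60 per group, P = 0.73: SE = 0.0811 and 0.15/SE = 1.851. Φ(1.851 − 1.645) = 58.2%; Φ(1.851 − 1.960) = 45.7%.
- 60 per group, P = 0.591: SE = 0.0898 and 0.15/SE = 1.671. Φ(1.671 − 1.645) = 51.1%; Φ(1.671 − 1.960) = 38.6%.
- 54 per group (10% lost): one-sided 0.05 falls from 54.4% to 47.6%; two-sided 0.05 falls from 41.9% to 35.4%.

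The planning rate therefore accounts for about 7 points in each comparison.

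**5. The effect of the rate alone.** Take a trial correctly sized at 73%, with 109 per group and one-sided 0.05. At P = 0.591, SE = √(0.4834/109) = 0.0666, 0.15/SE = 2.252, and Φ(2.252 − 1.645) = 73%, against the intended 80%.

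**6. Range.** The true control rate is unknown. With 60 per group at two-sided 0.05, power runs from 37.9% at P = 0.55 to 68.6% at P = 0.87. It stays below 80% throughout.

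**The case against.** The strongest reply is that 59.1% is not an exact match either. Its source includes steroid-resistant patients, whereas this trial enrols steroid-dependent disease only. The article gives neither the size of that source nor its treatment duration. This stands: 59.1% is the closer of the two cited rates, and no more than that.

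The case against 87% also has limits. The article does not say whether those patients were off steroids, so the difference in outcome rests on the Discussion's wording. More than 6 months against 24 weeks is a small gap in time. What keeps its force is the selection of patients who stayed on the drug, and the absence of any description of the source as steroid-free or steroid-dependent.

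Three stronger readings are tempting, and the article does not support them.

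- **That the planning rate explains the whole shortfall from 80%.** It does not. Power with 60 per group is already 58% or 46% at P = 0.73. Even at P = 0.87 and two-sided 0.05 it is only 68.6%.
- **That the Background's third figure confirms 59.1%.** There, "61% of patients were able to maintain clinical remission after 5 years of azathioprine therapy". But that cohort had inflammatory bowel disease, not only ulcerative colitis; the outcome is clinical remission, not stated to be steroid-free; and the horizon is 5 years. It fails the same tests as the 87%.
- **That a 15-point margin is laxer at 59.1%.** This depends on the scale. The relative loss of success is larger (15/59.1 = 25% against 15/73 = 21%). The margin is tighter on the odds scale (odds ratio 0.546 for 59.1% to 44.1%, against 0.511 for 73% to 58%) and on failure risk (55.9/40.9 = 1.37 against 42/27 = 1.56).

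It can also be said that the calculation has to be redone anyway. That is true, but a recalculation that kept 73% would carry this weakness forward.

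**Conclusion.** The point holds as a secondary defect of the sample-size calculation. The 73% averages two figures that the article itself describes differently, without a reason, and only the lower one is described with this trial's endpoint and a close population. Planning on 59.1% raises the required number by about 23% and lowers the power of 60 per group by about 7 points, to 51% (one-sided 0.05) or 39% (two-sided 0.05). The remaining distance to 80% belongs to the confusion of per-group and total numbers and to the one-sided constant.

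The figures assume equal true rates in both arms, the stated 15-point absolute margin, the normal approximation and, for the 60-per-group values, no loss to follow-up. They do not show that the true control rate is 59.1%. They show that the closest rate the article cites does not support the stated 80%.

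**What to change.** In the Sample size section, base the calculation on 59.1% as the closest cited rate, and say that its source also includes steroid-resistant patients. Leave the 87% out of the planning rate, and keep 73% only as a sensitivity case labelled optimistic. State the required number per group and the actual power of the 120 patients at both rates, with one significance level and the constant that belongs to it.

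The cost is a rewording of one section. It calls for no added enrolment and no new data. The drawback is that the stated power becomes less favourable, and an inconclusive noninferiority result would have to be read in that light.

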### Data management and statistical analysis

Data recorded in printed case report forms are kept in locked cabinets. Data will be double-entered on electronic case report forms by two persons. Frequency, median, and mean ± standard deviation of the steroid-free remission rate and the mean withdrawal time of steroids will be used for descriptive statistics. Student’s *t* test and analysis of variance will be employed using continuous variables with a normal distribution. The Mann–Whitney *U* test and Kruskal–Wallis test will be used for continuous variables with abnormal distributions, such as health-related quality of life and inflammation markers. A chi-square test or Fisher’s exact test will be used for categorical variables, including the efficacy of endoscopic response and the degree of mucosal healing. Results will be analyzed as per intention-to-treat. All data will be analyzed by an independent statistician using SAS 9.4. For all analyses, *P* < 0.05 is considered statistically significant.

To summarize the present study protocol, please see Additional file 1 for an overview of enrollment, interventions and assessments, and Additional file 2 for an overview of the Standard Protocol Items: Recommendations for Interventional Trials (SPIRIT) checklist.

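### The sample size constant 12.365 belongs to a one-sided 0.05 test, but the protocol states a two-sided 0.05 level

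*Protocol article*

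**What the plan says.** The Sample size section of the protocol article declares the design ("This is a noninferiority trial") and sets the error rates: "For a two-sided significance level of 0.05 and power of 80"%. A parenthesis repeats α = 0.05 and β = 0.2 and gives a margin δ of 0.15. The control remission rate is taken from two cited studies, 59.1% and 87%, of which "the average rate is about 73"%. The formula is printed as "n=12.365\times P\left(1-P\right)/{\delta}^2", that is, 12.365 × P(1 − P)/δ². After an allowance for loss ("Considering a 10% loss to follow-up") the total is 120, with 60 per group.

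The section on data management and statistical analysis adds only a general rule: "For all analyses, *P* < 0.05 is considered statistically significant". It does not say whether that level is one-sided or two-sided. No one-sided 0.05 test and no 90% confidence interval appears anywhere in the article.

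**The concern.** The significance level and the constant stand in the same calculation and should imply each other. They do not: the words describe a two-sided 5% level, while the constant is built with the one-sided 5% quantile.

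Two things depend on which is meant. The first is the decision rule. Noninferiority at two-sided 0.05 is judged by a 95% confidence interval against the 0.15 margin, and at one-sided 0.05 by a 90% interval. A result whose 90% interval clears the margin but whose 95% interval does not could be read either way. If the analysis follows the formula, the nominal chance of a false noninferiority claim is 5%, twice the 2.5% implied by the words. The second is power. If the analysis follows the words, the formula does not deliver the stated 80%.

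The trial is open-label (Discussion) and was still enrolling at publication (Trial status), so the level should be settled before the outcome data are examined.

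**Working it through.** **Inputs, all from the Sample size section:** α = 0.05, stated as two-sided; power 80%; δ = 0.15; P = 0.73 in both groups (the formula assumes no true difference); loss 10%; 60 per group.

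**Step 1: where the constant comes from.** For two equal groups with a common rate P, the number per group is n = 2(z_α + z_β)² × P(1 − P)/δ².
- One-sided 0.05, 80% power: 2(1.6449 + 0.8416)² = 12.365. This is the printed constant.
- Two-sided 0.05 (one-sided 0.025), 80% power: 2(1.9600 + 0.8416)² = 15.698.
- Ratio: 15.698/12.365 = 1.27.

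If 12.365 is kept with 1.960, the implied power is Φ(√(12.365/2) − 1.960) = Φ(0.527) = 70.1%.

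**Step 2: the plan's own figure.** P(1 − P) = 0.73 × 0.27 = 0.1971 and δ² = 0.0225.
- 12.365 × 0.1971/0.0225 = 108.3, so 109 after rounding up.
- With 10% loss: 108.3/0.9 = 120.4, or 108.3 × 1.1 = 119.1.

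The number 120 therefore comes from the one-sided constant. The factor 2 for two groups is already inside that constant, so 108.3 is a number per group, yet 120 was used as the total. That is a separate error, and the stated 60 per group follows from the formula at neither level.

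**Step 3: the number at the stated level.** 15.698 × 0.1971/0.0225 = 137.5, so 138 per group before loss. With 10% loss this is 154 per group (138/0.9) or 152 (138 × 1.1).

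**Step 4: power.** Power = Φ(δ/√(2P(1 − P)/n) − z_α), normal approximation:

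| n per group | One-sided 0.05 | Two-sided 0.05 (one-sided 0.025) |
|---|---|---|
| 109 (formula, before loss) | 80.2% | 70.3% |
| 60 (planned) | 58.1% | 45.6% |
| 54 (planned, after 10% loss) | 54.4% | 41.9% |

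Exact enumeration at one-sided 0.025 gives 70.9% for 109 per group and 80.3% for 138 per group, so the approximation is adequate.

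**Step 5: sensitivity to P.** Over the two cited rates, per group before loss:

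| P | One-sided 0.05 | Two-sided 0.05 |
|---|---|---|
| 0.591 | 133 | 169 |
| 0.73 | 109 | 138 |
| 0.87 | 63 | 79 |

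The 27% gap does not depend on P, apart from rounding.

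**The case against.** The best defence is that only the word two-sided is wrong. A noninferiority comparison has one direction. The parenthesis gives α = 0.05 without a side, and the constant and the number 120 both fit one-sided 0.05. On that reading the authors planned a one-sided 5% test and the slip is verbal. This is possible, but nothing else in the article supports it, and the reader cannot tell which was meant. Even on this reading the text has to change.

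A second point is that a planning constant does not set the analysis level. If the analysis uses a 95% interval, the risk of a false claim stays near 2.5% and only power suffers. An analysis plan that is not shown may fix this. That is correct, and it is why the 5% risk is stated only for the case in which the analysis follows the formula. The general rule on P values does not help either way, because it names no side.

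A third point is that most of the fall to 42–46% power belongs to the confusion of per-group and total numbers. This also stands: with 60 per group, power at one-sided 0.05 is already only 58%. The sidedness mismatch accounts for the further step to 46%, about 12 points, or for the step from 80% to about 71% with 109 per group.

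**Conclusion.** The stated level and the printed constant contradict each other, and nothing in the article reconciles them. Taken alone, the mismatch is worth 138 against 109 patients per group, or about 70–71% power in place of 80% if the formula's own 109 were evaluable. Combined with the separate per-group/total error, the planned 60 per group gives about 46% power at the stated level, and 42% with 54 evaluable.

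These figures assume equal true remission rates of 0.73 in both groups, the 0.15 absolute margin, 1:1 allocation and the usual correspondence between two-sided 0.05 and one-sided 0.025 for noninferiority. The contradiction itself rests on none of the rate assumptions, because it lies in the constant. The plan is wrong as written.

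**What to change.** Preferred: keep the two-sided 0.05 level, state that noninferiority will be judged by the 95% confidence interval against the 0.15 margin, and replace 12.365 with 15.698. Because that formula gives 138 per group before loss, it cannot stand above 60 per group with 80% power still claimed. If the enrolment target stays at 120, replace the 80% with the power it delivers: about 46% with 60 evaluable per group and 42% after 10% loss.

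Alternative: say openly that the test is one-sided at 0.05 with a 90% confidence interval, and remove two-sided from the Sample size section. The constant then stands, but 60 per group still gives only about 58% power (54% after loss), so the power statement must change here too.

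In either case, correct the per-group/total error in the same revision, since changing the constant alone does not repair the sample size. The cost is a few words, one constant and one restated power figure, with no extra patients required. The price is a less favourable power statement.

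### The sample size formula gives a number per group, but its result is used as the trial total, so 120 patients give about 54% power (one-sided 0.05) instead of the stated 80%

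*Protocol article*

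**What the plan says.** The Sample size section states "This is a noninferiority trial". From two cited azathioprine remission rates, 59.1% and 87%, it takes the midpoint: "the average rate is about 73" per cent. It gives a "two-sided significance level of 0.05 and power of 80" per cent, sets δ at 0.15, and prints the formula n = 12.365 × P(1 − P)/δ². It does not print the value of n, and does not say whether n is per group or in total. The next sentence is "Considering a 10% loss to follow-up, the sample size is 120 cases", with 60 in each group.

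The Methods/Design section repeats the size: the 120 patients "will be recruited and allocated into two groups, with 60 individuals per group". The Abstract also gives 120 as the number to be randomized, so the figure is not a slip in one place.

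**The concern.** A formula for comparing two proportions can be written for one group or for the whole trial, and the two differ by a factor of 2. The printed constant shows which version is in use. If it is the per-group version, treating the result as a total halves the trial.

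Power for the primary outcome is a central design claim. If the claim is wrong by this factor, a trial of two truly equivalent treatments has roughly even odds, or worse, of showing noninferiority, and a failure to show it could be misread as evidence of inferiority. The opposite misreading is also open. The Primary outcome measure section moves on to withdrawal time when the remission rates do not differ significantly, and in a trial this small a non-significant difference says little about whether the rates are similar.

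**Working it through.** **Inputs**, all from the Sample size section: P = 0.73, δ = 0.15, power 80%, constant 12.365, loss 10%, 60 per group.

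**1. Reproduce the plan's figure.**
12.365 × 0.73 × 0.27 / 0.15² = 12.365 × 0.1971 / 0.0225 = 108.3.
108.3 / 0.9 = 120.35.
So 120 is the formula's n after the loss allowance.

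**2. Identify the constant.**
With n in each group and a common rate P, the variance of the difference is 2P(1 − P)/n. Solving for n gives
n per group = 2 (z₁₋α + z₁₋β)² P(1 − P)/δ².
With z₀.₉₅ = 1.645 and z₀.₈₀ = 0.842 the multiplier is 12.365, which matches every printed digit. The multiplier for a total would be 4 (z₀.₉₅ + z₀.₈₀)² = 24.73. The formula's n is therefore per group.

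**3. Required size.**
- One-sided 0.05 (the level in the constant): 109 per group, 218 evaluable. After 10% loss, 109/0.9 = 121.1, so 122 per group and 244 in total. Without intermediate rounding, 2 × 120.35 = 240.7.
- Two-sided 0.05 as stated (one-sided 0.025): the multiplier is 2 (1.960 + 0.842)² = 15.70, giving 138 per group, 154 after loss, 308 in total.

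The planned 120 is about half of the first total and 120/308 = 39% of the second.

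**4. Power of the planned trial, equal true rates of 73%.**
Power = Φ(δ/SE − z₁₋α), with SE = √(2 × 0.1971/n).
- n = 54 (60 less 10%): SE = 0.0854.
- n = 60: SE = 0.0811.

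| Per group | One-sided 0.05 | Two-sided 0.05 |
|---|---|---|
| 54 | 54% | 42% |
| 60 | 58% | 46% |
| 109 | 80% | 70% |

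Exact binomial enumeration of the rule that the Wald confidence limit must lie above −15 points gives 55% and 43% with 54, and 58% and 46% with 60. With 109 per group at one-sided 0.05 it gives 80.5%, so the formula delivers its stated power only when n is read as per group.

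**5. Precision.**
With 60 per group and both observed rates at 73%, the 95% interval has half-width 1.96 × 0.0811 = 15.9 points and would miss the margin. The 90% interval, which corresponds to one-sided 0.05, has half-width 1.645 × 0.0811 = 13.3 points and would meet it.

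**6. Margin at which 80% power would hold.**
(z₁₋α + z₁₋β) × SE gives 21 points (one-sided 0.05) or 24 points (two-sided 0.05) with 54 per group, and 20 or 23 points with 60.

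**7. Sensitivity to P over the cited range, one-sided 0.05.**
- P = 0.591: 133 per group needed before loss; power 48% with 54, 51% with 60.
- P = 0.87: 63 per group needed before loss; power 75% with 54, 79% with 60.

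No rate in the cited range reaches 80%.

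**The case against.** The article never prints 108 and never says whether n is per group or total, so the step from one to the other is reconstructed. That is true, but the constant matches the per-group formula to every digit, and 108.3/0.9 gives 120. Other formulas tried with the stated inputs did not give 54 or 60 per group.

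The Discussion expects the herbal group to do better than azathioprine, and an advantage would raise power. If its true rate were 78% (an assumption; the article gives no figure), 60 per group would have about 82% power at one-sided 0.05 and 72% at two-sided 0.05. This limits the near coin-flip description to equal rates. It does not rescue the calculation, which uses one common P and assumes no advantage.

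The description of the trial as half the required size holds for the one-sided level in the constant, not for the two-sided level in the text. This stands as a second inconsistency in the same paragraph. It makes the shortfall larger, not smaller.

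The Data management and statistical analysis section specifies intention-to-treat, which favors 60 per group over 54 as the denominator. That is a fair point. It changes 54% to 58%, or 42% to 46%, and leaves the conclusion as it is.

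**Conclusion.** The concern holds. The formula yields 108.3 per group; the plan uses this as the total and enrolls half the patients that its own formula requires. The stated 80% power is wrong. At equal true rates of 73% and a 15-point margin, it is 54% to 58% at one-sided 0.05 and 42% to 46% at two-sided 0.05, depending on whether 54 or 60 per group are analyzed. These figures rest on the article's own P, δ and loss allowance and on the normal approximation, which exact enumeration supports. The article prints the formula, the inputs and the result together, so an unseen analysis plan could not reconcile them. This must be fixed.

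**What to change.** Rewrite the Sample size paragraph:

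- State that the formula gives 109 per group before loss.
- Reconcile the two-sided 0.05 label with the constant 12.365, which is for one-sided 0.05. State one level and use it throughout.
- If enrollment stays at 120, replace 80% with the true power: about 54% (one-sided 0.05) or 42% (two-sided 0.05) with 54 evaluable per group, or 58% and 46% if all 60 are analyzed. Add, for information only and without changing the 15-point margin, that 80% power would hold only for a margin of about 21 or 24 points with 54 per group.
- If the sponsor wants to keep 80% power, the total becomes about 244 (one-sided 0.05) or 308 (two-sided 0.05). The Trial status section says enrollment was continuing, so this choice was still open.
- Commit to reporting the primary result as a difference with its confidence interval. State that failure to show noninferiority will not be read as inferiority, and that a non-significant difference will not be read as equivalence. This fits the Abstract, which presents the findings as groundwork for later confirmatory trials.

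Restating the power costs one paragraph and a much less favorable figure, with no extra patients. Keeping 80% power means roughly doubling the trial, or more.
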